### Sample size calculation

Following a review of retrospective studies, the PPV for diagnosing cMM/SM1 using the JES classification was 55.7% [3]. In addition, a recent prospective study showed that the PPV of cMM/SM1 was 47% [13]. Because the PPV for cMM/SM1 based on the standard-depth evaluation is calculated using the same formula as that used for the accuracy, the accuracy for cMM/SM1 based on this study’s standard-depth evaluation is set at 50%. Because the accuracy was 77.7% in a previous study when considering the size of the B2 vessel area [13], it is assumed that considering the size and morphological type of the B2 vessel area would result in an improved accuracy of at least 15% in this study. The research group agreed that a 15% improvement in accuracy is clinically meaningful for improving the preoperative evaluation of tumor invasion depth. Therefore, assuming that the accuracy for the hypothetical-depth assessment is 65%, which is obtained by adding a 15% improvement to the accuracy of the standard-depth evaluation of 50%, when considering the size and morphological type of the B2 vessel area, the required lesion number is determined using an accurate test for the binomial distribution with a two-sided alpha error of 0.05, power of 90%, and the required lesion number of 121 lesions. After considering a dropout rate of approximately 10%, the necessary lesion number is calculated as 135.

### Planned statistical analyses

The main analysis for the primary endpoint, which is performed after all data associated with the endpoint are fixed after registration, aims to verify whether the accuracy can be improved by considering the size and macroscopic type of the B2 vessel area in addition to the standard-depth evaluation based on the JES classification. Suppose the diagnostic accuracy of the standard-depth assessment is statistically improved compared with that of the standard-depth evaluation. In that case, we will conclude that the hypothetical-depth review is a more useful diagnostic method. Suppose the accuracy of the hypothetical-depth evaluation does not significantly exceed that of the standard-depth evaluation. In that case, it can be concluded that standard-depth evaluation remains a useful diagnostic method. The overall two-sided significance level is set at 5%.

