## Discussion

Tumor invasion depth significantly impacts the selection of treatment for superficial esophageal cancer. Diagnosing preoperative tumor invasion depth is paramount because physical invasiveness significantly differs among treatments. However, the diagnostic yield of the JES classification for preoperative depth diagnosis is insufficient, particularly for cMM/SM1 cancer. A multicenter prospective study evaluating the diagnostic value of endoscopic ultrasonography (EUS) after magnifying endoscopy showed that adding EUS did not improve the accuracy of the tumor invasion depth diagnosis [16, 17]. This prospective study can establish a new approach for preoperative tumor invasion depth diagnosis based on high-level evidence, ultimately optimizing the process of diagnosing cT1 esophageal cancer.

Improving the PPV of cMM/SM1 is a pressing concern in the JES magnifying endoscopic classification. However, this study designated the PPV as a secondary endpoint because special attention is required when evaluating its improvement. There are specific patterns in which the overall diagnostic performance may deteriorate even if the PPV shows improvement. For instance, the PPV may increase when categorizing low-confidence cases as cEP/LPM or cSM2-3 instead of cMM/SM1, but the overall diagnostic performance may decrease. Therefore, we set accuracy as the primary endpoint for monitoring diagnostic performance. Nevertheless, even if the primary endpoint shows significant improvement, the clinical significance of considering the size and macroscopic type of the B2 vessel area is limited if the PPVs are substantially lower in the hypothetical-depth evaluation than in the standard-depth evaluation. Therefore, we will interpret the study results after confirming a higher percentage of PPVs for cMM/SM1 through the hypothetical-depth review compared with the standard-depth evaluation.

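### A non-significant superiority test is read as showing that the standard-depth evaluation is useful, which the plan has no means of showing

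*Protocol article*

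**What the plan says.** The decision rule is in the Planned statistical analyses section of the protocol article. The stated aim is to find out whether adding the size and macroscopic type of the B2 vessel area improves accuracy over the standard evaluation. Two branches follow.

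- **Success.** The condition reads: "Suppose the diagnostic accuracy of the standard-depth assessment is statistically improved compared with that of the standard-depth evaluation". The consequence is: "In that case, we will conclude that the hypothetical-depth review is a more useful diagnostic method".
- **Failure.** The condition reads: "Suppose the accuracy of the hypothetical-depth evaluation does not significantly exceed that of the standard-depth evaluation". The consequence is: "In that case, it can be concluded that standard-depth evaluation remains a useful diagnostic method".

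The Sample size calculation section assumes 50% accuracy for the standard evaluation and 65% for the hypothetical one, calls a 15-point gain clinically meaningful, and gives a "two-sided alpha error of 0.05, power of 90%, and the required lesion number of 121 lesions", raised to 135 for about 10% dropout.

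On the standard method itself, the Abstract calls its accuracy for B2 lesions insufficient, the Background says it needs improvement, and the Discussion states that "the diagnostic yield of the JES classification for preoperative depth diagnosis is insufficient, particularly for cMM/SM1 cancer".

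**The concern.** The failure branch turns the absence of a significant difference into a positive finding about the comparator. To conclude that the standard evaluation is useful, the plan would need either a minimum accuracy that counts as useful or a margin within which the two methods count as equivalent. It has neither. The conclusion also sits badly with the protocol's own reason for the study, which is that the standard evaluation performs poorly in exactly these lesions.

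At stake is what may be claimed after a null result. Followed literally, the rule lets the existing classification be endorsed on data that are compatible with the full targeted improvement.

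**Working it through.** **Inputs.** Standard accuracy 50%, hypothetical accuracy 65%, two-sided alpha 0.05, power 90%, 121 evaluable lesions, about 10% dropout (all from Sample size calculation). Discordance between the two evaluations is not given.

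**Step 1: reproduce the plan's figure.** Take an exact binomial test of the hypothetical accuracy against a fixed 50%, rejecting when the upper tail is at most 0.025. At n = 121 the critical count is 72 (59.5%):

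- P(X ≥ 72 | 121, 0.50) = 0.0225
- P(X ≥ 72 | 121, 0.65) = 0.912

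Power first reaches 90% at n = 114 and does so again at 119, but it falls below 90% at 115–118 and at 120. From 121 on it stays at or above 90%. With dropout, 121 / 0.90 = 134.4, rounded up to 135. Both stated numbers reproduce.

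**Step 2: how often the failure branch is reached under this test.** The probability is P(X ≤ 71 | 121, p):

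| True hypothetical accuracy | Gain over 50% | Chance of a null result |
|---|---|---|
| 65% | 15 points | 8.8% |
| 62.5% | 12.5 points | 21.8% |
| 60% | 10 points | 41.7% |
| 55% | 5 points | 81.7% |
| 50% | 0 | 97.7% |

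**Step 3: what a null result is compatible with.** The largest non-significant count is 71/121 = 58.7% (two-sided p = 0.069), with exact 95% CI 49.4% to 67.6%. The interval contains the targeted 65%.

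**Step 4: what is learned about the standard.** In a test against a fixed 50%, the observed number of correct standard diagnoses does not enter at all. In a paired comparison only the difference enters. In neither case does non-significance depend on the standard reaching any particular accuracy. If the standard performs as assumed, say 60/121 = 49.6%, its exact 95% CI is 40.4% to 58.8%, and nothing in the protocol says whether that counts as useful.

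**Step 5: sensitivity to the test.** Suppose a paired exact McNemar test is used instead. For total discordance D and a gain of 0.15, the proportion gained is (D + 0.15)/2 and the proportion lost is (D − 0.15)/2. At n = 121:

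| Assumed D | Gained / lost | Power | Chance of a null result |
|---|---|---|---|
| 0.2 | 0.175 / 0.025 | 0.971 | 3% |
| 0.3 | 0.225 / 0.075 | 0.837 | 16% |
| 0.4 | 0.275 / 0.125 | 0.713 | 29% |
| 0.5 | 0.325 / 0.175 | 0.609 | 39% |
| 0.6 | 0.375 / 0.225 | 0.527 | 47% |

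**The case against.** **The word 'remains' may only mean that practice stays as it is.** The Discussion supports this milder reading: it describes an unsuccessful trial as one in which the hoped-for clinical effect is not achieved and exploratory work follows, with no claim that the standard is validated. That limits how far the authors are likely to press the sentence. It does not rescue it, because the rule says that usefulness can be concluded, which is an inference from the data.

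**The success branch.** Its condition names the standard method on both sides, and a reader might infer that the rule is broken there too. The documents do not support that. The stated aim, the consequence attached to the condition, the failure condition and the Abstract all show that hypothetical versus standard is meant. It is a wording slip that needs correcting, not a fault of design.

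**The PPV statement in the Discussion.** It says the clinical significance of an accuracy gain is limited "if the PPVs are substantially lower in the hypothetical-depth evaluation than in the standard-depth evaluation", and that results will be interpreted after confirming a higher PPV for cMM/SM1. A reader might infer a second success rule that competes with the one based on accuracy. But the Discussion explains why PPV was deliberately made secondary and places this reading on top of the primary result. At most, a cross-reference is missing.

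**The size.** A reader might take one row of the McNemar table, such as 39% at a discordance of 0.5, as the rate of wrongly endorsing the standard. Neither that test nor that discordance is in the protocol, so only the range can be given, and as an assumption.

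**Conclusion.** The failure branch is wrong as written: non-significance does not show that the standard-depth evaluation is useful, and nothing else in the plan does. This rests on the text alone and holds whichever test compares the two accuracies.

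The size depends on the test. Under the exact binomial test against 50% that reproduces the 121 lesions, the unsupported conclusion would follow in 8.8% of trials with a true 15-point gain and in 41.7% with a true 10-point gain. The range of about 3% to 47% for a 15-point gain assumes a paired exact McNemar test and discordance of 0.2 to 0.6.

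The endpoint, the data collected and the sample size are unaffected.

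**What to change.** Replace the failure sentence with wording such as:

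> Otherwise, improvement over the standard-depth evaluation has not been shown; the difference in accuracy and its 95% CI are reported, and no conclusion on the usefulness of the standard-depth evaluation is drawn.

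In the same edit:

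- Correct the success condition so that it compares the accuracy of the hypothetical-depth evaluation with that of the standard-depth evaluation.
- Add a cross-reference to the PPV interpretation already given in the Discussion, without turning PPV into a new formal success criterion.

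The cost is a few reworded sentences and a weaker claim after a null result. The 121 evaluable and 135 registered lesions stay as they are.

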#### Analysis of the primary endpoint

The calculation formula for the standard-depth evaluation is: (lesions diagnosed as cMM/SM1 and pMM/SM1 [B]) / (total lesions [A + B + C]) (Table 3), and for the depth evaluation, [(lesions diagnosed as cEP/LPM and pEP/LPM [a]) + ((lesions diagnosed as cMM/SM1 and pMM/SM1 [e]) + (lesions diagnosed as cSM2-3 and pSM2-3 [i]))] / (total lesions [a + b + c + d + e + f + g + h + i]) (Table 4). A point estimate is calculated for accuracy, and a 95% confidence interval is calculated based on the exact binomial distribution. The corresponding *p*-value is also calculated.

**Table 3 Tab3:** Relationship between standard depth evaluation and histological depth diagnosis

	pEP/LPM	pMM/SM1	pSM2-3
cMM/SM1 (B2 vessel)	A	B	C

$$\begin{array}{l}\mathrm{Accuracy}\;\mathrm{of}\;\mathrm{standard}-\mathrm{depth}\;\mathrm{evaluation}\;(\%)\\=(\mathrm{number}\;\mathrm{of}\;\mathrm{lesions}\;\;\mathrm{diagnosed}\;\mathrm{as}\;\mathrm{cMM}/\text{SM}1\;\mathrm{and}\;\mathrm{confirmed}\;\mathrm{as}\;\mathrm{pMM}/\text{SM}1)/(\mathrm{total}\;\mathrm{number}\;\mathrm{of}\;\mathrm{lesions})\times100=\lbrack\text{B}\rbrack/\lbrack\text{A}+\text{B}+\text{C}\rbrack\text{x}100\end{array}$$

*MM* Muscularis mucosa, *SM1* Upper third of the submucosal layer, *EP/LPM* Epithelial/lamina propria

**Table 4 Tab4:** Relationship between hypothetical depth evaluation and histological depth diagnosis

	pEP/LPM	pMM/SM1	pSM2-3
cEP/LPM (B2 vessel area ≤ 4 mm)	a	b	c
cMM/SM1 (B2 vessel area between 4–10 mm without additional findings^a^)	d	e	f
cSM2-3 (B2 vessel area ≥ 10 mm or macroscopic type 0-I/0-III in B2 vessel area)	g	h	i

^a^Additional findings: B2 vessel area ≤ 4 mm, B2 vessel area ≥ 10 mm, macroscopic type 0-I/0-III in B2 vessel area

$$\begin{array}{l}\mathrm{Accuracy}\;\mathrm{of}\;\mathrm{hypothetical}-\mathrm{depth}\;\mathrm{evaluation}\;(\%)\\=(\lbrack\mathrm{number}\;\mathrm{of}\;\mathrm{lesions}\;\mathrm{diagnosed}\;\mathrm{as}\;\mathrm{cEP}/\mathrm{LPM}\;\mathrm{and}\;\mathrm{confirmed}\;\mathrm{as}\;\mathrm{pEP}/\text{LPM})+(\mathrm{number}\;\mathrm{of}\;\mathrm{lesions}\;\mathrm{diagnosed}\;\mathrm{as}\;\mathrm{cMM}/\text{SM}1\;\mathrm{and}\;\mathrm{confirmed}\;\mathrm{as}\;\mathrm{pMM}/\text{SM}1)+(\mathrm{number}\;\mathrm{of}\;\mathrm{lesions}\;\mathrm{diagnosed}\;\mathrm{as}\;\mathrm{cSM}2\;\mathrm{or}\;\mathrm{deeper}\;\mathrm{and}\;\mathrm{confirmed}\;\mathrm{as}\;\mathrm{pSM}2\;\mathrm{or}\;\mathrm{deeper}\rbrack)/(\mathrm{total}\;\mathrm{number}\;\mathrm{of}\;\mathrm{lesions})\times100.\\=(\text{a}+\text{e}+\text{i})/(\text{a}+\text{b}+\text{c}+\text{d}+\text{e}+\text{f}+\text{g}+\text{h}+\text{i})\mathrm x100\end{array}$$

*MM* muscularis mucosa, *SM1* upper third of the submucosal layer, *EP/LPM* epithelial/lamina propria

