**Methods:**

This multicenter prospective observational study will include patients diagnosed with MM/SM1 esophageal squamous cell carcinoma based on the Type B2 vessels of the JES classification. The tumor invasion depth will be evaluated using both the standard JES classification (standard-depth evaluation) and the JES classification with additional findings (hypothetical-depth evaluation) for the same set of patients. Data from both endoscopic depth evaluations will be electronically collected and stored in a cloud-based database before endoscopic resection or esophagectomy. This study’s primary endpoint is accuracy, defined as the proportion of cases in which the preoperative depth diagnosis matched the histological depth diagnosis after resection. Outcomes of standard- and hypothetical-depth evaluation will be compared.

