## Methods

### Study design

This is a multicenter prospective observational study. Endoscopic examinations will be performed in 13 hospitals in Japan. Tumor invasion depth will be evaluated based on only the JES classification (standard-depth evaluation) and the JES classification with additional findings (hypothetical-depth evaluation) for the same patients (Fig. 1). The study protocol will be performed following the Declaration of Helsinki and is approved by the Ethical Review Board of Shizuoka Cancer Center (IRB approval number: T2022–53–2022-1–2). The trial is registered in the Clinical Trials Registry of the University Hospital Medical Information Network (UMIN-CTR) as UMIN000051145. The date of the first registration was 23/5/2023.

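### The primary hypothesis compares two accuracies on the same lesions, but the primary analysis describes inference on one accuracy only, and the sample size points to a test against a fixed 50%

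*Protocol article*

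**What the plan says.** The protocol article, under Study design, has each tumour assessed by the standard evaluation and by "the JES classification with additional findings (hypothetical-depth evaluation) for the same patients". The abstract adds: "Outcomes of standard- and hypothetical-depth evaluation will be compared".

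Under Planned statistical analyses, the conclusion rests on the difference between the two methods. The failure branch begins: "Suppose the accuracy of the hypothetical-depth evaluation does not significantly exceed that of the standard-depth evaluation". The success branch names the standard evaluation on both sides, evidently a slip, so the direction of the hypothesis has to be read from the failure branch. The overall level is two-sided 5%.

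Under Analysis of the primary endpoint, both accuracies are defined as quantities observed in the study: B/(A+B+C) from Table 3 for the standard evaluation, and (a+e+i) over all lesions from Table 4 for the hypothetical one. The inference offered is: "A point estimate is calculated for accuracy, and a 95% confidence interval is calculated based on the exact binomial distribution". A corresponding p-value follows, with no null hypothesis attached.

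Under Sample size calculation, accuracy for the "standard-depth evaluation is set at 50" per cent, and the calculation proceeds "assuming that the accuracy for the hypothetical-depth assessment is 65" per cent. Then "the required lesion number is determined using an accurate test for the binomial distribution with a two-sided alpha error of 0.05" and 90% power, giving 121 lesions, or 135 after about 10% dropout. The same section cites 55.7% (retrospective) and 47% (prospective) as sources for the standard accuracy.

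**The concern.** The question is whether one method beats another on the same lesions. An exact binomial interval for an accuracy, with its p-value, concerns one proportion. It can be turned into a test only by supplying a fixed reference value, and the only such value in the document is the 50% used for planning.

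A test against 50% answers whether the hypothetical evaluation beats 50%, not whether it beats the standard evaluation in these lesions. The standard accuracy is estimated in the study, and the document's own sources for it span 47% to 55.7%. If it lies above 50%, a method that adds nothing can be declared an improvement. If it lies below 50%, a real improvement can be missed. The study's only confirmatory conclusion depends on this p-value.

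**Working it through.** **Inputs.** From Sample size calculation: standard accuracy 50%, hypothetical accuracy 65%, two-sided alpha 0.05, power 90%, 121 lesions, 135 with dropout, source values 47% and 55.7%. Not in the document: the proportion of lesions on which exactly one method is right (the discordance). With accuracies of 50% and 65% it can lie anywhere between 15% and 85%; results are shown for 20% to 50%.

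**Step 1: reproduce the 121.** One-sample exact binomial test, null 0.50, alternative 0.65, 0.025 per tail. The critical count r is the smallest with P(X ≥ r | n, 0.50) ≤ 0.025.
- n = 121: r = 72 (72/121 = 59.5%), upper-tail error 0.0225, power P(X ≥ 72 | 121, 0.65) = 0.912.
- n = 120: r = 72, power 0.892.
- Power also reaches 0.90 at n = 114 and 119, but 121 is the smallest n from which it stays there.
- Dropout: 121/0.9 = 134.4, rounded up to 135.

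Both stated numbers reproduce, with the comparator treated as a known constant. Two independent proportions would need 227 per group, so that is not the source of 121.

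**Step 2: behaviour of that test for the real question.** Suppose both methods have the same true accuracy p. Improvement is declared with probability P(X ≥ 72 | 121, p):

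| True accuracy of both methods | Probability of declaring improvement |
|---|---|
| 47% | 0.004 |
| 50% | 0.023 |
| 52% | 0.059 |
| 53% | 0.089 |
| 55.7% | 0.227 |

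The nominal value is 0.025. For power, a standard accuracy of 47% with a true 15-point gain gives 62%, and P(X ≥ 72 | 121, 0.62) = 0.746.

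**Step 3: the paired test.** Every enrolled lesion is cMM/SM1 by the standard evaluation, so the standard is right exactly in the pMM/SM1 column of Table 4 (b, e, h). The hypothetical evaluation is right in a, e and i.
- Only the hypothetical is right: a + i.
- Only the standard is right: b + h.
- Accuracy difference: [(a + e + i) − (b + e + h)]/n = [(a + i) − (b + h)]/n.

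Exact McNemar tests a + i as binomial with probability 0.5 out of a + i + b + h. At n = 121 its upper-tail error is 0.015 to 0.019 for 20% to 60% discordance, whatever the standard accuracy.

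**Step 4: power of the paired test at 121 lesions, 50% versus 65%.** With discordance s, the two discordant probabilities are (s + 0.15)/2 and (s − 0.15)/2.

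| Assumed discordance | Power at 121 | Lesions for 90% power |
|---|---|---|
| 20% | 0.97 | 90 |
| 25% | 0.91 | 119 |
| 30% | 0.84 | 143 |
| 40% | 0.71 | 193 |
| 50% | 0.61 | 241 |

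**Step 5: illustration with assumed counts.** Take standard 67/121 and hypothetical 74/121. The test against 50% gives p = 0.018. Exact McNemar depends on the assumed split of discordant lesions: 7 vs 0 gives p = 0.016, 8 vs 1 gives 0.039, 13 vs 6 gives 0.17, 26 vs 19 gives 0.37. The ordering can reverse. With standard 57/121 and hypothetical 71/121, the test against 50% gives p = 0.069, while McNemar gives 0.007 (19 vs 5) or 0.029 (25 vs 11).

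**The case against.** The strongest reply is that the analysis section never says the p-value is against 50%. That figure appears only as a planning assumption, and the decision rule speaks of the standard evaluation, not a benchmark. This stands: a reader might infer that the plan states a one-sample test against 50%, but the text does not. The fixed 50% is inferred from the reproduced sample size and from the binomial interval being attached to an accuracy. The error rates in Step 2 therefore apply only if that test is used.

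One could add that exact McNemar is itself a binomial test and would need about 119 lesions at 25% discordance, close to 121. But no discordance is stated anywhere, and the binomial interval is placed on the accuracy, not on discordant lesions. That reading has no support in the text.

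It is also fair to say that an article condenses the full protocol. For that reason the lack of an interval for the difference is not counted as a separate defect. The mismatch remains, because the article has a section devoted to the primary analysis and the method given there does not fit the hypothesis stated just above it.

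Finally, the 22.7% is the upper end of a range. At 47% the error is well below nominal.

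**Conclusion.** The point holds and needs correcting before the primary analysis. The hypothesis is a paired difference between two observed accuracies; the described inference concerns one accuracy, with no null value named. The sample size points to a test against a fixed 50%. Used that way at 121 lesions, the test's chance of declaring an improvement that does not exist runs from 0.4% to 22.7% across the document's own 47% to 55.7% range, against a nominal 2.5%. Power for a true 15-point gain is 0.75 if the standard is at 47%. If some other null is intended, the primary test is not defined.

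Two stronger readings are not supported. The error rate is not always inflated: that depends on the true standard accuracy. Nor would a paired test usually give a less favourable p-value: that depends on the observed standard accuracy and the discordance, and Step 5 shows both directions with assumed counts.

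**What to change.** Name the primary test as a two-sided 5% exact McNemar test on Table 4, a + i versus b + h. Report the accuracy difference [(a + i) − (b + h)]/n with a 95% confidence interval for paired proportions. Keep the two exact binomial intervals as descriptive. Correct the success sentence so that it names the hypothetical-depth evaluation.

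No new data are needed, since Table 4 already holds every cell, and the main analysis runs only after the endpoint data are fixed, so the test can still be specified beforehand.

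The cost is in the power statement. The 121 lesions were sized for a different test, and the document gives no discordance. One must be assumed and justified, and the 90% claim restated: it holds at 121 lesions only if discordance is about 25% or less. Above that, the sponsor must either accept the lower power openly or enrol more lesions (143 evaluable at 30%, 193 at 40%, before dropout).
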